### Ethical Considerations

This study has been approved by the University of Hawaii Institutional Review Board (IRB; 2022-00909). We will only collect data from voluntary participants who sign an informed consent (parents) and assent (children) document during the intake session of the study. Participants whose videos will be shared for the 20 crowdsourcing tasks used to filter workers will be contacted by the study team to have a thorough discussion about the planned use of those videos. Workers who are qualified to rate the remaining videos for ≥1 question will be required to complete The Health Insurance Portability and Accountability Act training and The Collaborative Institutional Training Initiative training and will be required to encrypt their laptops using whole disk encryption. These workers will be added to the IRB protocol and will become official members of the study team after thorough training.

Although we will require participants to consent to sharing videos with crowd workers who have undergone thorough training, the clinical translation of this diagnostic system will require a more scalable approach that is sensitive to privacy concerns. We will experiment with privacy-preserving alterations to the curated videos to obfuscate identifiable information from the videos without degrading the feature-tagging performance of workers. Examples include pitch shifting the audio, which will allow workers to understand the content of the speech, and pixelating the video, which will obscure the participant’s background and face but would still allow workers to observe body movement patterns. We will measure the extent to which each privacy-preserving mechanism degrades the answers to each question.

We will deidentify the participant data and anonymize any personally identifiable information. All the data will be immediately uploaded to our secure and encrypted server on Amazon Web Services (AWS) [50], which is Health Insurance Portability and Accountability Act–compliant. A fully anonymized version of the data set will be released to researchers only after signing a data use agreement, which will be approved by the University of Hawai‘I Data Governance Office.

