**Figure 2 figure2:**
[figure not shown]
Feature extraction and quantification of behaviors relevant to neuropsychiatric diagnostics. LSTM: Long Short-Term Memory network.

For complex social features beyond the scope of automated ML-powered computational processing, we will deploy a novel crowdsourcing framework consisting of a crowd worker profiling phase, followed by a study data tagging step. In the first phase, we will post 20 tasks on Amazon Mechanical Turk, each presenting a video acquired through pilot testing of the gamified social data collection platform, followed by a series of multiple-choice questions corresponding to items from the diagnostic criteria for ADHD and ASD, as defined by the DSM-5. Each task will correspond to a separate video, and there will be 4 videos per diagnostic category used to quantify worker abilities. Worker responses will be compared against the Clinical Global Impression gold standard ratings provided by our collaborators in the Department of Psychiatry at the University of Hawai‘i. Crowd workers who align with the ratings of clinical experts on at least 1 behavioral feature, where alignment is defined as <1 categorical ordinal deviation per 2 videos, will be recruited to label the final study data from 400 participants. Recruited workers will only label those features for which their alignment with clinicians was demonstrated during the profiling phase as shown in Figure 3.

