#### Evaluation

To assess the effectiveness of the crowdsourcing pipeline, we will compare the performance of crowd workers before and after their recruitment. The preliminary data show that crowd workers who answer similarly to clinicians during filtering continue to perform in a similar manner on new, unseen videos. We will also measure crowdsourcing metrics such as latency to starting a task, interrater reliability, any decline in performance with increased ratings, and the completion rate for all assigned tasks. To evaluate the privacy-preserving mechanisms, we will randomly assign each worker to a single privacy condition per video, only asking them to rate the unaltered videos after the ratings for the privacy condition have been provided. We will measure the mean deviation from clinician answers per privacy condition for each question.

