### Multicondition Diagnostics With Adaptive Input Querying

#### Description

We will develop DL models for the multilabel classification of ADHD and ASD, which can emit four possible outcomes: (1) ADHD, (2) ASD, (3) ADHD and ASD, and (4) neither condition. The models will also output the behavioral characteristics that led to the final classification decision by producing the 95% CI of each behavior as derived from both crowd workers and automated computational models. This will involve synthesizing multiple sources of inputs and communicating the result to the end user in a manner that is understandable to the patient or the caregiver. The confidence scores will enable the model to adaptively request more data from the patient and to be specific about which types of data are needed.

To derive an interpretable quantification of each behavioral feature, we will collect clinical categorical ratings of each behavior by licensed psychiatrists at the University of Hawai‘i at Mānoa. We will compensate the psychiatrists for their service and will use the mean of the crowd worker responses as a baseline method for deriving the interpretable quantification of each behavior. Although this method could be sufficient, it is possible that crowd workers have varying levels of rating abilities depending on the qualities of the video and the qualities of the crowd workers themselves. Therefore, we will explore the use of the crowdsourced ratings themselves combined with crowdsourcing metrics derived from worker performance and the computationally generated behavioral features as collective inputs into an ML model for each behavior. Such metrics will include the time spent by each worker providing the annotations for the video, worker rating history for each question, and variability in the worker’s answers across videos and within a particular video. It has been previously shown that these crowdsourcing metrics and similar metrics have predictive power in a crowd worker’s annotation quality [11]. We will test whether the ML model is a better predictor than the crowdsourced ratings alone. The loss function for the ML model for individual behaviors will optimize with respect to the mean clinician rating per behavior.

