#### Evaluation

The diagnostic ML model will be evaluated using balanced classification metrics including AUROC, area under the precision-recall curve, balanced accuracy, precision, recall (sensitivity), *F*_1_-score, and specificity. Performance and CIs will be derived through Monte Carlo cross-validation, with each data split consisting of 300 participants in the training set, 50 participants in the validation set, and 50 participants in the test set. All splits will contain a balance with respect to the 5 diagnostic classes, age, gender, race, and ethnicity.

To evaluate the effectiveness of the active learning querying system, we will run post hoc simulations comparing the random selection of new data against targeted requests using active learning. We will train the classification system with 12 sessions of data, hold out the remaining 9 sessions, and plot the performance of each metric against the number of additional samples acquired using both active learning and random selection of data segments.

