### Novel Crowd-Powered and Traditional ML-Based Feature Extraction

We have conducted a series of preliminary studies testing the use of crowdsourcing for precision behavioral health, demonstrating that although there is a high degree of variability in crowd workers’ innate ability to rate complex social behaviors in unstructured home videos [10], there exists a small fraction of crowd workers on platforms such as Amazon Mechanical Turk who consistently rate in alignment with licensed clinical experts [48,49]. In a study, we demonstrated that a group of 40 crowd workers filtered from an original pool of >1000 workers was able to rate behaviors that, when fed into a classifier trained on clinician records, achieved an AUROC of 0.9904 for one set of features and 0.9872 for another feature set [42]. Our experience of receiving approval from university IRBs and data privacy offices as well as obtaining consent from families to share their videos with crowd workers mitigates any risks related to this novel process.

After applying privacy-preserving modifications to the videos, such as pitch shifting the audio downward and using face detection to box out the child’s face, the performance of the model remained >0.95 for both AUROC and area under the precision-recall curve [42]. Although these results show promise for predicting autism in a binary task, they are likely to decline in accuracy when expanding to include ADHD as a diagnosis too. These studies provide strong evidence to support the proposed worker matching procedure, which will enable the more nuanced feature space required for multicondition classification. The prior experience in developing automated pipelines for managing crowd workers will help streamline the development of the crowd management scripts.

The feasibility of the automatic feature extraction steps comes from the existing packaging of the required functionalities into Python libraries and the high documented performance of these tools. All the ML-powered feature extractors we have used are well documented.

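### Mean deviation from clinician answers, with no sign convention and no correction for chance, can miss loss of information caused by the privacy alterations on some items

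*Protocol article*

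**What the plan says.** Methods, Ethical Considerations, describes experiments with alterations that hide identity. Pitch shifting and pixelation of the face and background are given as examples, and the aim is stated: "We will measure the extent to which each privacy-preserving mechanism degrades the answers to each question".

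Methods, Novel Crowd-Powered and Traditional ML-Based Feature Extraction, Evaluation, gives the design. Workers are randomised to one privacy condition for a video, with the team "only asking them to rate the unaltered videos after the ratings for the privacy condition have been provided". The outcome follows: "We will measure the mean deviation from clinician answers per privacy condition for each question". No sign convention is given. The same paragraph also says "We will also measure crowdsourcing metrics such as latency to starting a task, interrater reliability, any decline in performance with increased ratings", but for the crowdsourcing pipeline as a whole and not by privacy condition.

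Three other places bear on the point:
- The Description in the same section uses deviation to select workers, "where alignment is defined as <1 categorical ordinal deviation per 2 videos".
- The Results section on feature extraction reports that, after alteration in preliminary work, "the performance of the model remained >0.95 for both AUROC and area under the precision-recall curve". It adds that this was a binary autism task and that accuracy will probably fall once ADHD is included.
- Methods, Multicondition Diagnostics With Adaptive Input Querying, Evaluation, lists AUROC and other metrics for the diagnostic model, with no mention of privacy condition.

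**The concern.** A mean deviation measures how close answers lie to the clinician's. It does not measure whether they follow the clinician's from one video to the next. A worker who can no longer see a behavior may fall back on the commonest answer, and on an item where one answer dominates, that habit costs little distance. If the deviation is signed, errors in opposite directions also cancel.

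The failure is plausible here. Pixelation hides the face, while Table 2 lists emotion evocation, eye contact and face gaze among the targeted behaviors. An alteration could be reported as nearly harmless on an item for which it has removed the information. The result matters because Ethical Considerations ties clinical translation to a more scalable approach that protects privacy.

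**Working it through.** The plan states no figure for the privacy comparison, so there is none to reproduce. It also gives no item prevalences, scale lengths or worker error rates. Those below are assumptions, shown over a range.

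**1. Signed reading, present/absent item.** With prevalence p, sensitivity Se and specificity Sp:

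mean signed deviation = (1−p)(1−Sp) − p(1−Se).

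- A worker who guesses 'present' at rate p, without looking, has Se = p and 1−Sp = p. The result is (1−p)p − p(1−p) = 0 at every prevalence.
- A worker with Se = Sp = 0.80 scores 0.20(1−2p), which is 0.16 at 10%, 0.12 at 20% and 0 at 50%.

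The guesser scores as well or better. In a simulation over seven assumed rating distributions (400,000 ratings each), guesses drawn from the clinicians' own distribution had a signed mean of about 0.00 throughout. An informed worker had 0.00 to 0.17.

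**2. Absolute reading, present/absent item.**

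mean absolute deviation = p(1−Se) + (1−p)(1−Sp).

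Always answering 'absent' (Se = 0, Sp = 1) gives p. Guessing at rate p gives 2p(1−p). Se = Sp = 0.80 gives 0.20p + 0.20(1−p) = 0.20.

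| Prevalence | Always 'absent' | Guess at rate p | Se = Sp = 0.80 | Kappa, Se = Sp = 0.80 |
|---|---|---|---|---|
| 10% | 0.10 | 0.18 | 0.20 | 0.35 |
| 20% | 0.20 | 0.32 | 0.20 | 0.49 |
| 30% | 0.30 | 0.42 | 0.20 | 0.56 |
| 50% | 0.50 | 0.50 | 0.20 | 0.60 |

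For the last column, observed agreement is 0.80 and the worker's 'present' rate is q = 0.20 + 0.60p. Chance agreement is pq + (1−p)(1−q), and kappa = (0.80 − chance)/(1 − chance). At 20%, q = 0.32, chance = 0.064 + 0.544 = 0.608 and kappa = 0.192/0.392 = 0.49. Both uninformed workers have kappa 0 at every prevalence. Kappa separates the workers in every row, whereas absolute deviation does not.

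**3. Absolute reading, four-level ordinal item.** The informed worker is assumed exact 60% of the time, one step up 20% and one step down 20%, held within the scale. The expected deviation is 0.20 at either end of the scale and 0.40 in between.

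- Ratings 25/25/25/25: informed 0.50×0.20 + 0.50×0.40 = 0.30. Uninformed: 1.00 for a constant second-level answer, 1.25 for uniform guessing. The loss is plain.
- Ratings 75/15/7/3: informed 0.78×0.20 + 0.22×0.40 = 0.24. Constant lowest answer: 0.15 + 0.14 + 0.09 = 0.38. The gap is small, and 0.38 is below the 0.5 per video implied by the worker-alignment rule (1 step/2 videos).
- Ratings 85/10/4/1: informed 0.86×0.20 + 0.14×0.40 = 0.23. Constant lowest answer: 0.10 + 0.08 + 0.03 = 0.21. The loss is hidden.

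Over the seven simulated distributions, correlation with the clinician was 0.54 to 0.88 for the informed worker and about 0 for uninformed workers who varied their answers. It was undefined for a constant answer.

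**4. Does the unaltered rating rescue the measure?** Suppose a worker has Se = Sp = 0.80 on the unaltered video and always answers 'absent' on the altered one. Altered minus unaltered deviation is 0.20 − 0.20 = 0 at 20% prevalence and 0.10 − 0.20 = −0.10 at 10%. The comparator inherits the weakness.

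**The case against.** The strongest reply is that the measure works in many settings. That stands: with absolute deviation, total loss is obvious on items with spread-out ratings (0.30 against 1.00 to 1.25) and on present/absent items from about 30% prevalence upward. A reader might infer that the measure can never detect loss of information, and the documents do not support that. Nor can rarity be presumed: 300 of the 400 participants are to have ASD, ADHD or both, and the questions come from the DSM-5 criteria for those conditions. Against this, videos are cut into 3-minute clips, and Related Work notes that not every defining symptom need be present. How often a behavior appears per clip is therefore unknown in both directions.

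The signed reading is also the less likely one. The worker-alignment rule makes sense only as a distance and uses the same word. What remains there is a missing definition.

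A reader might also infer that the cost of privacy in diagnostic accuracy has never been examined. It was, in the preliminary binary autism work. The article is condensed and the privacy work is exploratory, so leaving out a classifier result by condition is not an error in itself.

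Finally, a reader might infer that ratings of altered videos feed the main crowd feature, because the plan "will use the mean of the crowd worker responses as a baseline method" and names no exclusion. The text is silent either way. It introduces the altered-video ratings only to evaluate the privacy mechanisms, so this supports no more than a request for clarification.

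**Conclusion.** The point holds in a limited form. The only measure tied to privacy condition is undefined as to sign and is not corrected for chance. If signed, it can miss loss of information through cancellation. If absolute, it can miss loss on items where one category dominates: a tie at 20% prevalence and a reversal at 10% in the present/absent example, and 0.21 against 0.23 in the 85/10/4/1 example. On evenly used scales it performs well. These sizes rest on assumed prevalences, scale lengths and worker error rates, and on an uninformed worker who gives the commonest answer.

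Separately, the article describes no evaluation of what the alterations cost in four-outcome accuracy, although its authors expect lower accuracy there than in the binary task. This is a worthwhile, inexpensive improvement to a secondary component. It does not threaten the main diagnostic evaluation.

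**What to change.** 1. In the feature-extraction Evaluation, define the deviation as absolute.
2. Beside it, report weighted kappa or a rank correlation with the clinician rating for every question and privacy condition, as a paired change from the same workers' unaltered ratings. Count a constant answer as no information and do not drop it as missing.
3. For videos rated both altered and unaltered, score the diagnostic classifier on each set of ratings and report the paired AUROC difference.
4. As a clarification only, state which ratings form the mean crowd response.

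Items 1, 2 and 4 need only analysis and wording, since altered and unaltered ratings are already planned. Item 3 is limited to videos rated both ways. The article does not say that every participant's video will be rated under every condition, so wider coverage could need more ratings. Splitting by condition leaves fewer ratings per video and less precise estimates. Because the unaltered version always comes second, the paired change also includes any effect of having seen the video before, and the report should say so.

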### Multicondition Diagnostics With Adaptive Input Querying

#### Description

We will develop DL models for the multilabel classification of ADHD and ASD, which can emit four possible outcomes: (1) ADHD, (2) ASD, (3) ADHD and ASD, and (4) neither condition. The models will also output the behavioral characteristics that led to the final classification decision by producing the 95% CI of each behavior as derived from both crowd workers and automated computational models. This will involve synthesizing multiple sources of inputs and communicating the result to the end user in a manner that is understandable to the patient or the caregiver. The confidence scores will enable the model to adaptively request more data from the patient and to be specific about which types of data are needed.

To derive an interpretable quantification of each behavioral feature, we will collect clinical categorical ratings of each behavior by licensed psychiatrists at the University of Hawai‘i at Mānoa. We will compensate the psychiatrists for their service and will use the mean of the crowd worker responses as a baseline method for deriving the interpretable quantification of each behavior. Although this method could be sufficient, it is possible that crowd workers have varying levels of rating abilities depending on the qualities of the video and the qualities of the crowd workers themselves. Therefore, we will explore the use of the crowdsourced ratings themselves combined with crowdsourcing metrics derived from worker performance and the computationally generated behavioral features as collective inputs into an ML model for each behavior. Such metrics will include the time spent by each worker providing the annotations for the video, worker rating history for each question, and variability in the worker’s answers across videos and within a particular video. It has been previously shown that these crowdsourcing metrics and similar metrics have predictive power in a crowd worker’s annotation quality [11]. We will test whether the ML model is a better predictor than the crowdsourced ratings alone. The loss function for the ML model for individual behaviors will optimize with respect to the mean clinician rating per behavior.

To model the multilabel classification problem, we will create separate binary classifiers for ASD and ADHD. Each model will be optimized separately. In comparison with training distinct binary classifiers, a single model trained in a multitask learning setup is able to share parameters between the classification tasks. This helps the model focus on distinguishing features between conditions and has been found to reduce overfitting. We expect that the multitask setting will decrease the number of false-positive predictions by helping the model recognize features that overlap between conditions.

Using a sigmoid activation function for each independent classifier, the classification system will output a probability score for each diagnostic possibility as well as each of the behaviors defined by the DSM-5, which will be quantified by the system.

Using the output scores of the DL model, an active learning system will be developed that queries for additional data from the user in a targeted manner by suggesting the next game for the participant to play. For each participant, the algorithm will measure the confidence score of each behavioral symptom and produce a list of games for the user to play, sorted by the classifier’s mean uncertainty of the behavioral symptoms each game is designed to curate data for. Classifier uncertainty will be measured by the entropy of each classifier’s output vector. As neural networks are inherently uncalibrated, we will apply a method published by Kuleshov et al [60] based on isotonic regression to calibrate the probability estimates before measuring uncertainty.

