We hypothesize that diagnostic ML models that incorporate both human-annotated features acquired through crowdsourcing (to generate a complex feature space with respect to social human behavior) and automatically extracted features (to provide objectivity when possible) will outperform models that use only automatically extracted features or only human-provided features, as there will likely be nonlinear interactions between features. This complex feature space will allow the classification model to simultaneously distinguish 4 possible outcomes: only ASD, only ADHD, both ASD and ADHD, or neither condition. To support efficient and reliable feature tagging by workers, we will develop novel crowdsourcing algorithms for quantifying the behavioral tagging strengths and weaknesses of each worker. The algorithms will dynamically assign workers to tasks based on their tagging history. We will alter each video to provide privacy protection for the participants while still allowing reliable tagging. To facilitate the acquisition of sufficiently structured data, we will develop a broadly accessible gamified web platform for curating socially enriched video and audio clips in a targeted manner. We will use active learning algorithms to adaptively query for additional data in cases where the presence of a particular symptom is unclear from the current set of ML features and crowdsourced ratings. Each of these innovations (crowdsourcing algorithms, privacy-preserving video alterations, gamified social data capture systems, and active learning algorithms to dynamically query needed data), although useful for the field of precision psychiatry individually, will be combined to create a novel diagnostic system with greater discriminative power than previously possible.

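### A win for the behavior-level ML model over the raw crowd mean cannot be credited to worker metrics or computed features, because only the model is fitted to clinician ratings

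*Protocol article*

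**What the plan says.** The comparison is set out in the Protocol article, Methods, Multicondition Diagnostics With Adaptive Input Querying, Description.

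- **Baseline.** The investigators "will use the mean of the crowd worker responses as a baseline method for deriving the interpretable quantification of each behavior".
- **Challenger.** One model per behavior takes "crowdsourced ratings themselves combined with crowdsourcing metrics derived from worker performance and the computationally generated behavioral features as collective inputs". The reason given is that worker ability may vary with the video and the worker, and that such metrics have been shown to predict annotation quality.
- **Training target.** "The loss function for the ML model for individual behaviors will optimize with respect to the mean clinician rating per behavior".
- **Test.** "We will test whether the ML model is a better predictor than the crowdsourced ratings alone".

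The section names no metric for this test and describes no model fitted to the crowd ratings alone.

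Workers are pre-selected (Novel Crowd-Powered and Traditional ML-Based Feature Extraction, Description) by agreement with clinicians, "where alignment is defined as <1 categorical ordinal deviation per 2 videos".

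**The concern.** The two sides differ in two respects: the challenger has more inputs, and it alone is trained on the target by which both are judged. The crowd mean, as described, is fitted to nothing. If crowd answers sit systematically above or below the clinicians', or are noisy because few workers rate a clip, a regression line on the crowd mean alone would bring them closer. The challenger gets that correction whether or not its extra inputs carry information.

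At stake is the interpretation of a win. The plan's rationale invites credit to the worker metrics and computed features, when the gain could be a shift or shrinkage that needs neither.

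**Working it through.** The plan gives no figure for this comparison, so there is none to reproduce. The check is a decomposition followed by simulation.

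**1. What fitting alone gains.** Let Y be the mean clinician rating, M the crowd mean and β the regression slope of Y on M. Then

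MSE(raw M) − MSE(best line in M) = (mean of M − mean of Y)² + (1 − β)² · Var(M).

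The first term is a shared offset. The second is shrinkage, which grows when few raters make M noisy. Neither involves worker metrics or computed features.

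**2. Whether an offset can survive worker selection.** Fewer than 1 category of deviation per 2 videos is fewer than 0.5 per video. Averaged over the 20 profiling videos, that is a total below 10. A worker one category too high on 9 videos and exact on the other 11 has deviation 9/20 = 0.45, all in one direction, and qualifies. The rule bounds a shared offset without removing it.

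**3. Simulation of held-out error.** Assumptions, none from the plan: a 0–3 item, mean of 3 clinicians, mean of 5 workers with noise SD 0.5, crowd slope 1, 10 extra inputs of pure noise, linear models and 400 runs. Training on 300 and testing on 50 participants is borrowed from the diagnostic model's splits ("300 participants in the training set, 50 participants in the validation set, and 50 participants in the test set").

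| Offset | MSE raw mean | MSE line on crowd mean | MSE full model | Full beats raw | Full beats line |
|---|---|---|---|---|---|
| 0 | 0.062 | 0.062 | 0.064 | 38% | 29% |
| 0.2 | 0.097 | 0.064 | 0.066 | 99% | 28% |
| 0.4 | 0.195 | 0.071 | 0.073 | 100% | 26% |

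The gain from fitting is 0.097 − 0.064 = 0.033 at offset 0.2 (formula: 0.2² = 0.040) and 0.195 − 0.071 = 0.124 at 0.4 (formula: 0.4² = 0.160). It falls short of the formula because the ends of the scale cut off part of the shift. Ten useless coefficients cost about 10/300 = 3.3% of the error: 0.064 × 1.033 = 0.066. The extra inputs made prediction slightly worse, and the whole gain over the raw mean is recalibration. Average break-even comes at an offset near √(0.064 × 10/300) = √0.0021 ≈ 0.05 category.

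These shares count a lower held-out error, not a significant test. Their reference level is the 26–29% in the last column, not 5%.

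**4. Simulation with the worker filter and a formal test.** The extra inputs were again noise. Workers were kept only if they met the alignment rule, and a one-sided 5% paired test was applied to squared errors. Two implementations of this design gave:

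| Average leniency before filtering | Full model beats raw mean |
|---|---|
| 0.4 category | 34–84%; 49–83% |
| 0.2 category | 7–52%; 18–78% |
| 0, with 3–5 raters | 0–7%; 2–8% |

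Against the same learner fitted to the crowd ratings only, the full model won in at most 2.5% of runs in both. In the first implementation, no leniency with one rater per clip gave 24–36% (shrinkage), and absolute error in the 0.4 case gave 2–60%.

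**5. Metric.** A linear recalibration cannot change a correlation. In the three settings of step 3, the noise-input model had the higher correlation in 25–30% of runs, in line with its reference level.

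**The case against.** The strongest reply is that the plan asks a practical question: is the simple mean good enough, or should a model replace it? For that choice, lower error from correcting leniency is a real improvement, and the raw mean is the right reference. That stands. A reader might go further and infer that the comparison is invalid, or that the raw mean should be dropped. The document supports neither, because the comparison answers the practical question soundly.

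A second reply is that the fusion idea is tested elsewhere. The Methods Overview hypothesizes that combined models "will outperform models that use only automatically extracted features or only human-provided features". That concerns the diagnostic models. It does not separate the inputs at behavior level, nor does the isotonic calibration of model probabilities before the querying step.

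Third, the phrase about ratings alone could cover a fitted ratings-only model, and a condensed article may leave such detail to the full plan. This is possible, but the only ratings-only method the section names is the unfitted mean. If a fitted model is intended, one sentence settles it.

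Fourth, the document reports no shared leniency. Bonuses for matching clinicians and the preliminary finding that filtered workers stay aligned on new videos both work against a large offset. This limits the likely size but excludes nothing, since the selection rule permits an offset.

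**Conclusion.** The point holds as one of attribution. The planned comparison shows which score is closer to clinicians. It does not show that worker metrics or computed features contributed, although they are the stated reason for the model.

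The size is conditional. On an error-type metric, a shared offset of a few tenths of a category, or a single rater per clip, can produce a win from recalibration or shrinkage alone. With an unbiased crowd and several raters, or with a correlation metric, there is little inflation. The plan does not state the metric for this test. Elsewhere it measures agreement as deviation from clinician answers, which makes an error-type metric plausible but not certain.

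A reader might infer that the model will win spuriously, or at the simulated rates. The document does not support that: rating scale, noise, offset and raters per clip are all assumed, and only the mechanism follows from the text. The evaluation of the diagnostic model is not affected.

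**What to change.** Keep the comparison with the raw crowd mean for the practical question. Add one arm: the same learner trained on the crowd ratings only, with the same loss, splits and clinician target. State that worker metrics and computed features are credited only if the full model beats this ratings-only model on the same held-out participants.

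The cost is one extra fit per behavior on data already planned, and a sentence in the plan. The downside is that the gain credited to the extra inputs may shrink.
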